## Abstract

**Background:**

Cardiovascular disease (CVD) is the most common complication and the leading cause of death in patients with chronic kidney disease (CKD). Accelerated atherosclerosis is a pathophysiological process that is vital to the occurrence of cardiovascular complications associated with CKD. Abnormal platelet activation is not only the leading cause of atherosclerosis but also plays a critical role in the occurrence of thrombotic events. Currently, antiplatelet drugs are commonly used as a secondary prevention strategy for high blood pressure, obesity, diabetes, and ischemic heart disease and can reduce the risk of CVD in the susceptible population. However, the benefits and evidence of using antiplatelet agents in patients with CKD remain controversial. This study aimed to determine whether antiplatelet therapy can safely prevent atherosclerosis in patients with CKD in the primary care setting.

**Methods/design:**

The ALTAS-CKD study is a multicenter, prospective, randomized, double-blind, placebo-controlled trial of 554 adult patients with stage 3–5 non-dialysis-dependent CKD recruited from 10 territory medical centers in China. A secured web-based computer randomization system will be used to administer aspirin 100 mg once daily or a matching inactive placebo for 36 months. The primary endpoint will be the occurrence of atherosclerosis, as measured by carotid ultrasonography. The secondary endpoints will be combined cardiovascular events, all-cause mortality, and 50% decrease in the estimated glomerular filtration rate.

**Trial registration {2a}:**

Current controlled trials number: ChiCTR1900021393. Registered on 18 February 2019.

## Introduction

### Background and rationale {6a}

The prevalence of chronic kidney disease (CKD) in western countries and China is reported to be 11% [1, 2]. Once CKD occurs, it may eventually progress to chronic renal failure and end-stage renal disease (ESRD) [3]. Cardiovascular disease (CVD) is the most common complication and the leading cause of death in patients with CKD and ESRD. The cardiovascular mortality rate in uremia patients ranges from 44 to 51% [4]. Moreover, the risk of cardiovascular mortality in patients with CKD stage 5D aged between 25 and 34 years is 100–150 times higher than that in other age groups [5]. Even in CKD patients aged 60 years and older, the CVD mortality is five times higher than that in the general population (participants were aged 18 years or older and from low- and middle-income countries) [6, 7]. Therefore, it is essential to clarify the critical mechanism underlying the development of cardiovascular complications in patients with CKD and establish an effective treatment.

Previous studies have indicated that CKD-induced atherosclerosis is the primary pathophysiological process underlying the occurrence of cardiovascular complications in patients with CKD. The acceleration of atherosclerosis in CKD patients causes plaque instability [8]. Consequently, arterial plaque rupture can easily result in thromboembolic diseases [9]. Abnormal platelet activation and progression play an essential role in the development of atherosclerosis and trigger the occurrence of physiological hemostasis and various diseases [10, 11]. Previous studies have found that the abnormal activation of platelets is not only a key role in thrombotic events but also the cause of atherosclerosis occurrence and development [12].

The relationship between CKD platelet activation and accelerated atherosclerosis has drawn considerable attention in recent years. Other researchers and our previous studies have found that abnormal platelet activation is manifested by an increase in platelet reactivity in CKD patients and animal models [13–15]. Previous extensive population-based studies have shown that atherosclerosis is highly prevalent in CKD patients, thus increasing the risk of cardiovascular and all-cause mortality. CKD patients have more severe atherosclerosis than age- and sex-matched controls from the general population [6]. The NEFRONA study has indicated that the incidence rates of carotid atherosclerosis are 50.8% in patients with CKD and 69% in diabetic patients with CKD [16]. Currently, antiplatelet drugs are widely used to prevent CVD, especially intravascular thrombosis. Antiplatelet drugs can reduce CVD deaths by 15% and CVD incidence by 20% in high-risk patients [17]. The American Heart Association recommended that antiplatelet drugs can be used as a secondary prevention strategy for patients with high blood pressure, muscular atrophy, obesity, diabetes, or a family history of ischemic heart disease [17]. Although antiplatelet drugs have been shown to reduce the risk of CVD in patients with CKD, the benefits and evidence of using antiplatelet agents in CKD patients remain unknown. A previous meta-analysis showed that antiplatelet drugs could reduce the risk of myocardial infarction in patients with CKD but were not associated with all-cause and cardiovascular mortality [18]. Simultaneously, the SWEDEHEART study demonstrated that dual antiplatelet therapy could reduce the risk of all-cause mortality, stroke, and reinfarction in acute coronary syndrome patients with CKD [19]. Aspirin is widely used and recommended as the first-line antiplatelet drug in the clinical setting. However, a previous meta-analysis indicated that aspirin had no apparent benefits on the primary prevention of CVD in the CKD population [20]. Thus, the efficacy and safety of antiplatelet therapy, like aspirin, in patients with CKD remain controversial. The evidence is not considered robust as previous researches were small sample cohort studies and lacked large clinical randomized controlled (RCT) studies. In addition, CKD patients were excluded or only those with mild CKD (CKD stages 1–2) were recruited in previous extensive RCT studies to assess the efficacy of antiplatelet therapy. Thus, the use of antiplatelet therapy in patients with CKD has fundamental clinical significance. Therefore, a prospective RCT trial must be performed to determine the significance of antiplatelet therapy in CKD patients.

### Objectives {7}

This study aimed to determine the efficacy and safety of aspirin for preventing atherosclerosis in patients with CKD stages 3–5.
To evaluate the effect of antiplatelet therapy on accelerated atherosclerosis in patients with CKDTo evaluate whether antiplatelet therapy can reduce cardiovascular events or mortality in patients with CKDMoreover, antiplatelet therapy is considered to be safe for patients with CKD.

### Trial design {8}

This study is a prospective, open, randomized, controlled multicenter study initiated by the Second Affiliated Hospital of the Army Medical University (Xinqiao Hospital) and approved by the ethics committee of Xinqiao Hospital. An exploratory design will be to investigate the efficacy and safety of aspirin for preventing atherosclerosis in patients with CKD stages 3–5. All eligible patients will be randomly assigned to either the aspirin group or the placebo group (Fig. 1).

**Fig. 1 Fig1:**
[figure not shown]
The study design and follow-up

### Eligibility criteria {10}

#### Participants

##### Inclusion criteria

According to the Kidney Disease: Improving Global Outcomes (KDIGO) guidelines, CKD refers to the abnormalities in the kidney structure or function or an estimated glomerular filtration rate (eGFR) of < 60 ml/min/1.73 m^2^ that persists for 3 months with or without kidney damage. The GFR was obtained by calculating the CKD-EPI using the following Cystatin C formula: eGFR=169 × Scr^-0.608^ × CysC^−0.63^ × Age^−0.157^ × (0.83 if female).Patients diagnosed with CKD stages 3–5 (non-dialysis dependent) aged 30–65 years (including those aged 30 and 65 years).Sex and ethnicity restrictions were not imposed.Patients without atherosclerosis in the common carotid artery as observed on the vascular ultrasound examination and no history of atherosclerosis in the carotid artery.An informed consent form from participants is required (Supplementary document).

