### Outcomes {12}

The primary outcome (see Table 1) is atherosclerosis at treatment endpoint (36 months).

**Table 1 Tab1:** Primary and secondary outcomes of the study

Outcome	Metric	Time point

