**Primary**		
**Atherosclerosis**	Occurrence rate of atherosclerosis	**36** months

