**Secondary**		
The combined cardiovascular events	Incidence	**36** months
All-cause mortality	Incidence	**36** months
eGFR decreased by 50%	the proportion of eGFR decreased by 50%	**36** months
Safety outcomes	Numbers	**36** months

Carotid ultrasonography will be used to screen for atherosclerosis. The bilateral carotid arteries will be analyzed by color Doppler ultrasound at a frequency of 10 MHz using a linear array transducer (Model Vinno 70; VINNO Technology (Suzhou) Co., Ltd., China) by an experienced sonographer. A smooth carotid artery is considered normal. An atherosclerotic plaque is defined as a focal structure encroaching into the arterial lumen by at least 0.5 mm or 50% of the surrounding intima-media thickness (IMT) value or with a thickness of > 1.5 mm, as measured from the media-adventitia interface to the intima-lumen interface [21]. Both atherosclerotic plaques and IMT are indicators of carotid atherosclerosis. The carotid ultrasonography will be performed at 6, 12, 24, and 36 months to identify the status of carotid atherosclerosis.

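### The ultrasound entry criterion names only the common carotid artery, while the primary outcome covers the bilateral carotid arteries and need not be new, so an undiagnosed lesion can count as an occurrence

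*Protocol article*

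**What the plan says.** Entry (Eligibility criteria {10}, Inclusion criteria): "Patients without atherosclerosis in the common carotid artery as observed on the vascular ultrasound examination and no history of atherosclerosis in the carotid artery". The criterion has two parts. The ultrasound part is limited to the common carotid. The history part covers the carotid artery generally, but can only act on disease that someone has already diagnosed.

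Outcome (Outcomes {12}, Table 1 and the text below it): the primary outcome is atherosclerosis at 36 months, with the metric "Occurrence rate of atherosclerosis". On the scan: "The bilateral carotid arteries will be analyzed by color Doppler ultrasound". No segments are listed. On timing: "The carotid ultrasonography will be performed at 6, 12, 24, and 36 months to identify the status of carotid atherosclerosis".

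Definition (same section): plaque has numeric limits. The wording begins "An atherosclerotic plaque is defined as a focal structure encroaching into the arterial lumen by at least 0.5 mm or 50% of the surrounding", where the percentage refers to the adjacent intima-media thickness (IMT); a thickness above 1.5 mm also qualifies. The text then adds: "Both atherosclerotic plaques and IMT are indicators of carotid atherosclerosis". No separate cut-off for IMT follows.

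Nowhere does the protocol say that an outcome lesion must be absent on the baseline scan, or must lie in a segment that was clear at baseline.

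**The concern.** The objective is prevention, so the primary event should be a lesion that was not there at randomization. The protocol secures this only indirectly, by requiring a clear artery at entry. That works only if the field cleared at entry is the field read at the end, and the two rules describe the field differently.

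A patient whose common carotid is clear, who has no known carotid disease, and who has a silent lesion elsewhere in the carotid meets the criterion as written. At 36 months the same lesion can be scored as an occurrence. Treatment cannot prevent a lesion that already exists, so each such patient is a case in whichever arm they fall. The observed difference shrinks, power falls, and part of the reported occurrence rate is disease present at entry.

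**Working it through.** **The plan's own figure.** Inputs from Sample size {14}: p0 = 0.40, p1 = 0.25, two-sided alpha 0.05, beta 0.10, 251 per group. The printed formula is

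n = [z_alpha √(2 p̄ q̄) + z_beta √(p1 q1 + p0 q0)]² / (p1 − p0)²

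with p̄ = 0.325, so 2 p̄ q̄ = 0.43875 and p1 q1 + p0 q0 = 0.1875 + 0.24 = 0.4275.

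- z_beta = 1.2816 (beta 0.10): n = 202.8, so 203 per group.
- z_beta = 1.645 (beta 0.05): n = 250.4, so 251 per group.

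The stated 251 therefore matches 95% power, not the stated 90%. That is a separate matter. It is noted here because it explains why the power figures below start at 95%.

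**Adding lesions present at entry.** Let f be the share of participants, equal in expectation in both arms, who have an undiagnosed lesion outside the common carotid that is scored at 36 months. The protocol gives no value, so f is an assumption. Take 40% and 25% as the new-onset rates among the rest:

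observed rate = f + (1 − f) × p

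power = Φ{ [d √n − 1.96 √(2 p̄ q̄)] / √(p1 q1 + p0 q0) }, where d is the difference in observed rates and n = 251.

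Example, f = 0.10:

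- Control 0.10 + 0.90 × 0.40 = 0.460; aspirin 0.10 + 0.90 × 0.25 = 0.325; d = 0.135.
- p̄ = 0.3925, so √(2 p̄ q̄) = 0.6906; √(0.2484 + 0.2194) = 0.6839.
- [0.135 × 15.843 − 1.96 × 0.6906] / 0.6839 = 1.148, so power is 87.5%.

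| f (assumed) | Control | Aspirin | Difference (points) | Control cases present at entry (f / control rate) | Power, 251 per group | n per group for 90% |
|---|---|---|---|---|---|---|
| 0% | 40.0% | 25.0% | 15.0 | 0% | 95.0% | 203 |
| 5% | 43.0% | 28.75% | 14.25 | 11.6% | 91.7% | 236 |
| 10% | 46.0% | 32.5% | 13.5 | 21.7% | 87.5% | 273 |
| 20% | 52.0% | 40.0% | 12.0 | 38.5% | 77.1% | 361 |

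With 249 evaluable per group (277 less 10%), power is 94.9%, 91.5%, 87.2% and 76.8%.

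**Sensitivity to how the 40% is read.** If the planned 40% control rate already includes lesions present at entry, and the relative effect 0.25/0.40 = 0.625 acts only on new ones, the aspirin rate is f + (0.40 − f) × 0.625. At f = 10% this is 0.10 + 0.30 × 0.625 = 28.75%. Power at 251 per group is then 87.9% at f = 5%, 75.8% at 10% and 41.6% at 20%. The protocol does not say which reading applies.

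**The case against.** The strongest defence is that the two fields may be the same in practice. Outcomes {12} says carotid ultrasonography serves to screen for atherosclerosis and then describes the bilateral scan. If the entry scan is done that way, a lesion outside the common carotid might be seen and excluded. Equally, a bilateral scan confined to the common carotids would fit the outcome wording. The flow chart is not shown and may settle it. All of this stands as a limit: the outcome text names no segments, so a reader who infers that the whole carotid tree is scored goes beyond it. But seeing a lesion at entry does not exclude the patient when the criterion names only the common carotid, and nothing in the outcome definition then removes the lesion.

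Four further inferences are tempting and not supported:

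- **Bias between arms.** Allocation is random and the study is described as double-blind, so lesions present at entry fall on both arms by chance. Any expected difference still comes from new lesions. The effect is dilution.
- **No protection against prior disease.** The history part of the criterion does exclude known carotid atherosclerosis; the gap is undiagnosed lesions only.
- **An event booked at month 6.** A scan takes place then, but the outcome is set at 36 months and the tests at 1, 2 and 3 years.
- **IMT turning old lesions into new ones.** The missing IMT cut-off affects entry and follow-up alike. The sentence may be descriptive, and plaque itself has numeric limits. It is a separate gap in the definition.

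The size is also open. At f = 5% power stays above the stated 90%, and the protocol's carotid atherosclerosis figures for CKD patients (50.8%, and 69% with diabetes) do not say how much lies outside the common carotid in patients with no known disease.

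**Conclusion.** The point holds as a mismatch between two stated rules. Followed as written, the protocol can count an undiagnosed lesion present at entry as an occurrence at 36 months, in either arm. Measured against the stated 90% power, the enlarged sample of 251 per group absorbs a share of 5% (91.7%) but not 10% (87.5%) or 20% (77.1%). These figures rest on an assumed f, on new-onset rates of 40% and 25% among patients free of such lesions, and on every such lesion being scored at 36 months. The loss is larger if the planned 40% already contains them. The documents do not show that power will in fact fall below 90%, because f is unknown. They do show that nothing in the outcome definition prevents it.

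**What to change.** - List the carotid segments once and use that list, with the numeric plaque definition in Outcomes {12}, for both the baseline scan and the outcome scans.
- Define the primary event as plaque by that definition at 36 months in a segment that was plaque-free on the baseline scan.
- State that IMT alone does not make a primary event, or give it one cut-off that applies at baseline and follow-up. A separate analysis of IMT as a continuous measure is optional.

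The cost is protocol wording and a segment field on the scan form. An ultrasound examination at entry is already required. If events are counted by segment, no one need be excluded, since every eligible patient has at least a clear common carotid in which a new plaque can be counted. If patients with any baseline plaque are excluded instead, there will be some screen failures, in a number that the documents do not allow one to estimate. Trial status describes the trial as not yet recruiting. The change belongs before the first baseline scan, because a segment not recorded then may not be recoverable later.

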##### Exclusion criteria

Patients who are unable to provide an informed consentPatients who are unable or unwilling to complete the process required by the researchPatients who are involved in other interventional clinical trialsPregnant or lactating womenPatients with previous cardiovascular diseases such as myocardial infarction, heart failure, and cerebral hemorrhagePatients with NYHA class III or IV heart failurePatients with cirrhosisPatients with HIV infection or AIDSPatients receiving chemotherapy or alkylating agents as treatment for malignant tumors in the past 2 yearsKidney transplant patientsPatients with deep venous thromboembolism before enrollmentPatients using aspirin, clopidogrel, or other antiplatelet drugs before enrollmentPatients with active bleeding or coagulopathy dysfunction

##### Who will obtain the informed consent? {26a}

The research investigator at each study location will obtain the informed consent and facilitate participant enrollment. Informed consent from participants will be required. The Patient Information Sheet contains the research background and purpose, research program, study procedures, voluntary principle, rights and responsibilities, expected risks and discomfort associated with the study, treatment measures for research-related damages and expected benefits of the participants, and the consent form explaining the above items in detail.

##### Additional consent provisions for collection and use of participant data and biological specimens {26b}

The collection, processing, and storing of biological specimens will be carried out in accordance with the clinical trial protocol, standard operating procedures, and principles of Good Clinical Laboratory Practice. The storage and use of specimens are described in detail in the patient’s informed consent form. All applicable institutional policies will be followed when handling or discarding specimens after completing all analyses.

### Interventions

#### Explanation for the choice of comparators {6b}

The efficacy and safety of aspirin for the prevention of atherosclerosis in CKD patients have not been proven by large clinical randomized controlled (RCT) studies. In addition, CKD patients were excluded, or only those with mild CKD (CKD stages 1–2) were recruited in previous extensive RCT studies to assess the efficacy of antiplatelet therapy. Thus, the use of antiplatelet therapy in patients with CKD has fundamental clinical significance.

#### Intervention description {11a}

##### Aspirin group

Aspirin regimen: an aspirin dose of 100 mg will be administered daily, and no dietary restrictions will be imposed; if the dose is missed, the medication will be re-administered and taken the next day according to the original plan.

Placebo group: Patients will receive a placebo pill, in which the appearance and shape are consistent with those of aspirin.

##### Consolidated drugs

High blood pressure should be treated with antihypertensive drugs (target blood pressure < 130/80 mmHg).Hypercholesterolemia is primarily treated with a statin, whereas hypertriglyceridemia is primarily treated with fibrate drugs.Low-molecular-weight heparin anticoagulants are preferred for anticoagulant treatment.Use of the following drugs is prohibited: non-steroidal anti-inflammatory drugs and macrolides such as clarithromycin and erythromycin.If the blood sugar level increases during the treatment period, oral hypoglycemic drugs will be administered as initial treatment; if necessary, insulin therapy will be provided as additional treatment.

#### Criteria for modifying or discontinuing intervention {11b}

Participants (1) who cannot tolerate aspirin, (2) in whom treatment was discontinued for more than 2 months due to various reasons, and (3) who will voluntarily withdraw from the study. Those who chose to withdraw from the study will receive appropriate treatment based on the judgment of each central investigator.

#### Strategies to improve adherence to interventions {11c}

Checkups, consultations, and the WeChat app will be used to improve compliance; other methods will also be adopted, such as monitoring and education during monthly appointments. The research team will also remind the participants regarding their upcoming appointment through phone calls or messages sent from the WeChat app.

#### Relevant concomitant care permitted or prohibited during the trial {11d}

During the trial, the participants have access to palliative supportive care for symptom relief, psychological support, and social support. Consolidated drugs could be used under the supervision of the research team. However, any other medical treatments that may influence the trial will be prohibited.

#### Provisions for post-trial care {30}

Post-trial care will not be planned. The possible risks are described in detail in the informed consent form. If any patient suffered harm during the trial, appropriate medical and nursing care will be provided, but not free of charge.

### Outcomes {12}

The primary outcome (see Table 1) is atherosclerosis at treatment endpoint (36 months).

**Table 1 Tab1:** Primary and secondary outcomes of the study

Outcome	Metric	Time point
**Primary**		
**Atherosclerosis**	Occurrence rate of atherosclerosis	**36** months
**Secondary**		
The combined cardiovascular events	Incidence	**36** months
All-cause mortality	Incidence	**36** months
eGFR decreased by 50%	the proportion of eGFR decreased by 50%	**36** months
Safety outcomes	Numbers	**36** months

Carotid ultrasonography will be used to screen for atherosclerosis. The bilateral carotid arteries will be analyzed by color Doppler ultrasound at a frequency of 10 MHz using a linear array transducer (Model Vinno 70; VINNO Technology (Suzhou) Co., Ltd., China) by an experienced sonographer. A smooth carotid artery is considered normal. An atherosclerotic plaque is defined as a focal structure encroaching into the arterial lumen by at least 0.5 mm or 50% of the surrounding intima-media thickness (IMT) value or with a thickness of > 1.5 mm, as measured from the media-adventitia interface to the intima-lumen interface [21]. Both atherosclerotic plaques and IMT are indicators of carotid atherosclerosis. The carotid ultrasonography will be performed at 6, 12, 24, and 36 months to identify the status of carotid atherosclerosis.

